**3. Materials and Methods**

Participants

Fifty young adults of both sexes, aged between 18-35 years will be recruited through wide dissemination on the campus of the Federal University of Rio Grande do Norte-UFRN. The sample size was determined with G * Power of the F test family (RM-ANOVA with intra-between interaction), considering a moderate to high effect size (f = 0.3) at α = 0.05 and 80% of power, as well as 60% correlation between repeated measures and considering loss of participants during the study being necessary at least 40 participants to attend these parameters.

Participants will be interviewed in advance and will complete a series of questionnaires to verify their eligibility for the study. Upon being elected to the study, they will be randomized into two groups proposed in this study.

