**Dosage of salivary cortisol**

Salivary cortisol dosages will be performed from samples collected on day 3 of the protocol. They will be made using commercial dosage kits from the company DRG Instruments GmbH (Germany).

The basic principle used by the kit is the competition ELISA, in which a microplate is sensitized with monoclonal antibodies (IgG) to cortisol. The reading of samples will be performed by spectrophotometry.

On day 1 of the protocol, the participant will answer the pre-intervention questionnaires and a blood sample will be collected for subsequent analysis of cortisol and BDNF.

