**Statistical analysis**

Initially, Kolgomorov-Smirnov normality tests will be applied to determine if the data obey a normal distribution. Once this prerequisite is met, Student's t test (parametric variables) or Mann Whitney U test (non-parametric variables) will be applied to detect the occurrence of significant differences within group and ANOVA to evaluate between groups differences. Spearman's correlation test will also be applied to test the occurrence of correlations between variables (anxiety, affect, stress and mindfulness, trait and state).

An exploratory and confirmatory factor analysis will be performed to verify the domains and association between the factors existing in the questionnaires. The internal consistency of the factors will be verified using Crombach's Alpha and only saturation values ​​greater than 0.4 for the eigenvalues ​​will be computed for the item's participation in the investigated domain.

For the analysis of plasmatic and behavioral markers, correlation tests and multivariate analysis will be used.

For all tests, the significance level (p value) less than or equal to 0.05 will be considered.

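### The analysis section pairs within-group tests with an ANOVA that names no baseline or group × time term, and so does not carry over the interaction used to size the trial

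*Protocol*

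**What the plan says.** Statistical analysis (Protocol) matches tests to comparisons. After a normality check, Student's t or Mann-Whitney U is to detect "significant differences within group and ANOVA to evaluate between groups differences". No covariate, change from baseline or group × time term is named. Plasma and behavioural markers also get correlation tests and a multivariate analysis that is not defined.

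Materials and Methods, Participants, sizes the trial on a different footing, an "RM-ANOVA with intra-between interaction" run in G*Power. Its inputs are f = 0.3, a 5% significance level, 80% power and a correlation of 0.6 between repeated measures. The result is given as "being necessary at least 40 participants to attend these parameters", and fifty are to be recruited.

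Pre-intervention values exist for most outcomes. Under Dosage of salivary cortisol: "On day 1 of the protocol, the participant will answer the pre-intervention questionnaires and a blood sample will be collected". That sample serves the cortisol and BDNF assays. Blood is drawn again after the intervention (Blood collection). The attention task is run before and after (Sustained Attention), and the questionnaires are given before, during and after (Questionnaires). Salivary cortisol differs: it is assayed from day 3 only, with one sample before the stress test and three after it.

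**The concern.** A significant change in one arm and a non-significant change in the other is not a test of whether the arms differ. Several measures are repeated (the attention task, heartbeat counting, the questionnaires), so practice effects and regression to the mean can move both arms together. The colouring control is there to absorb such shared change, and a within-arm test does not use it.

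The between-group ANOVA, as worded, need not use the day-1 value and is not said to be the interaction that justified the sample size. If it compares post values only, it ignores baseline data that the trial already pays for. For salivary cortisol, the section does not say how the four-sample response is to be compared between groups. At stake are whether the main claim rests on the randomised comparison and how precise that comparison is.

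**Working it through.** **Inputs.** From Participants: correlation ρ = 0.6, f = 0.3, two-sided α = 0.05, N = 40 and N = 50. Assumed: 1:1 allocation (20 or 25 per arm), equal SDs before and after, and paired within-group tests. The protocol does not say the t test is paired, and Mann-Whitney U is an independent-samples test. The size of any common change is not in the protocol, so a range is shown.

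**The plan's own figure.** The usual noncentral-F formula for the within-between interaction has λ = f²·N·m/(1 − ρ), with (m − 1) and (N − 2)(m − 1) degrees of freedom. The number of measurements m is not stated. For m = 2, 3, 4 and 5 the smallest even N with 80% power is 20, 16, 14 and 12. The stated 40 is not reproduced. That is a separate matter and does not decide this point.

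**Separate within-group tests when the arms change equally.** The SD of a paired difference is √[2(1 − 0.6)] = 0.894 SD. Let p be the power of the paired t test in one arm. The arms are independent, so the chance that only the mindfulness arm is significant is p(1 − p), and the chance that exactly one arm is significant is twice that.

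| Common true change | p (20 / 25 per arm) | Mindfulness only | Exactly one arm |
|---|---|---|---|
| 0 SD | 0.05 / 0.05 | 5% / 5% | 10% / 10% |
| 0.2 SD | 0.16 / 0.19 | 13% / 15% | 27% / 31% |
| 0.4 SD | 0.48 / 0.57 | 25% / 25% | 50% / 49% |
| 0.5 SD | 0.66 / 0.77 | 22% / 18% | 45% / 36% |
| 0.6 SD | 0.81 / 0.90 | 15% / 9% | 31% / 19% |
| 0.8 SD | 0.97 / 0.99 | 3% / 1% | 6% / 2% |

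Simulation of 40,000 trials per setting, for changes of 0 to 0.6 SD, agrees to within a percentage point. The misleading pattern is commonest when p is near one half.

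**Variance of the group contrast relative to post-only.**
- Post-only ANOVA: 1.00.
- Change score, which equals group × time for two time points: 2(1 − 0.6) = 0.80.
- ANCOVA on baseline: 1 − 0.6² = 0.64.

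ANCOVA saves 1 − 0.64 = 36% against post-only and 1 − 0.64/0.80 = 20% against the change score.

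**Power.** For a standardised group difference d and variance factor v, λ = N·d²/(4v), with 1 and N − 2 degrees of freedom (N − 3 for ANCOVA). The protocol does not say what f = 0.3 stands for, so two readings are shown.

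*f as a post-intervention group difference:* d = 2 × 0.3 = 0.6 SD.

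| Analysis | N = 40 | N = 50 | N for 80% |
|---|---|---|---|
| Post-only | 46% | 55% | 90 |
| Change score | 54% | 64% | 72 |
| ANCOVA | 64% | 74% | 58 |

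*f as the interaction effect with two time points:* each cell departs by 0.3 SD, so the difference in changes is 4 × 0.3 = 1.2 SD.

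| Analysis | N = 40 | N = 50 |
|---|---|---|
| Post-only | 96% | 99% |
| Change score | 98.5% | 99.6% |
| ANCOVA | 99.6% | 99.9% |

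On this second reading the choice of analysis hardly affects power.

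**The case against.** The strongest reply is that the only ANOVA the protocol specifies is the one in the sample-size paragraph. That ANOVA contains the group × time interaction and therefore uses the pre-intervention value; model terms are often left to a statistical analysis plan. A reader might infer that the planned ANOVA is definitely unadjusted. The document is silent on this, so the inference goes too far. What stands is that the analysis section does not name the interaction, and the two sections need to be reconciled.

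A reader might also infer that the treatment effect is to be judged by the within-group tests. The protocol does not say so: it gives between-group differences to the ANOVA. The risk lies in listing within-group tests alongside it without calling them descriptive.

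Other points on that side hold:
- Time-of-day drift is not a good argument. Sessions are in the morning, blood is drawn in a fixed window, and the attention task is always at the same hour.
- The rate at which exactly one arm is significant counts both directions. The misleading pattern in favour of mindfulness is half of it.
- After randomisation, post-only and change-score comparisons are unbiased, only less efficient.
- Baseline adjustment cannot apply to day-3 salivary cortisol, which has no pre-intervention value.

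**Conclusion.** The point holds as a gap in what the analysis section fixes. It lists within-group tests and a bare between-group ANOVA, and it leaves out the interaction on which the trial was sized. If within-group results were used to infer an effect, equal change in both arms would give a mindfulness-only finding in 1% to 25% of trials over common changes of 0 to 0.8 SD. This assumes ρ = 0.6, paired tests and 20–25 per arm.

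The 36% and 20% variance reductions follow from the protocol's own correlation, but the first applies only if the ANOVA is post-only. The power gain depends on how f = 0.3 is read: 19 percentage points at N = 50 against post-only (74 − 55), or 10 against the change score (74 − 64), if it means 0.6 SD; almost nothing if it is the interaction effect. The case for the change therefore rests first on valid inference and only conditionally on power.

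**What to change.** Rewrite the Statistical analysis section so that it agrees with the sample-size paragraph:

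- For each outcome with a pre-intervention value, the treatment effect is one between-group comparison of the post-intervention value adjusted for baseline (ANCOVA or an equivalent mixed model), reported as an estimate with a 95% confidence interval.
- Day-3 salivary cortisol is compared between groups by group × sample time over its four samples.
- Within-group changes are descriptive only.

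The sample-size paragraph should also say which effect f = 0.3 refers to and how many measurements were assumed.

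The cost is wording and about one degree of freedom per pre/post model. No new data are needed. Adjusting for sex and log-transforming cortisol are optional.

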With the diversity of works found in the literature about the application of mindfulness-based programs, there are three main lines where the studies are concentrated: attention training, benefiting people with attention deficit hyperactivity disorder or similar condition (ZYLOWSKA DEBORAH ACKERMAN MAY H YANG JULIE L FUTRELL NANCY L HORTON T SIGI HALE; PATAKI; SMALLEY, 2008), better emotional regulation from the recognition of automatic modes of thoughts or feelings in people with depression (KUYKEN et al., 2015), and o development of self-knowledge and improved resilience in the face of stressful situations in people with some mental disorder (DAVIS; SETH KURZBAN, 2012).

MBSR (specifically aimed at reducing stress) has been widely studied in healthy individuals or with some disease and its effect has been demonstrated on the neuroendocrine axis with short and long-term interventions (BROWN; WEINSTEIN; CRESWELL, 2012; CHIESA; SERRETTI, 2009; CRESWELL et al., 2014; DECKRO et al., 2002; O'LEARY; O'NEILL; DOCKRAY, 2015)

Creswell et al. in 2014 demonstrated that a 3-day MBSR exercise practice improved participants' perception of stress when compared to a control group. In this study, participants underwent the social stress test (TSST - Trier Social Stress Test) after the interventions and it was found that people who have a more pronounced mindfulness trait before the intervention have lower neuroendocrine axis reactivity to acute stress. However, compared to the control group, the group undergoing mindfulness practice had, in general, an increase in the level of salivary cortisol (CRESWELL et al., 2014). In fact, the mindfulness trait seems to influence cortisol levels and the individual's relationship with negative emotions, with those with a lower trait being more prone to emotional dysfunctions and those with a higher trait showing better adaptation to a stressful stimulus (BROWN; WEINSTEIN; CRESWELL, 2012; DAUBENMIER et al., 2014).

In a 6-week mindfulness-based program in students, was observed lower levels of perceived stress, anxiety, and depression (DECKRO et al., 2002).

In a systematic review about the relationship between mindfulness practice and cortisol levels, the authors report the impossibility of reaching a common conclusion about the results found. This is due to lack of randomization or methodological problems found in the studies. (O’LEARY; O’NEILL; DOCKRAY, 2015).

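### The arm comparison of day-3 salivary cortisol, which has no pre-training value, leaves out day-1 trait mindfulness, the baseline score that the protocol itself associates with cortisol reactivity

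*Protocol*

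**What the plan says.** Four places in the protocol bear on this.

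- **Outcome.** Under Dosage of salivary cortisol: "Salivary cortisol dosages will be performed from samples collected on day 3 of the protocol". Under Saliva, the four samples are one before the stress test and three at 15, 30 and 60 minutes after it. None precedes training.
- **Day-1 data.** The same dosage section adds: "On day 1 of the protocol, the participant will answer the pre-intervention questionnaires and a blood sample will be collected". The Questionnaires section lists the MAAS and the FFMQ among the scales given before, during and after the intervention.
- **Predictor.** The Introduction (Mindfulness-based programs) reports from an earlier 3-day study that "people who have a more pronounced mindfulness trait before the intervention have lower neuroendocrine axis reactivity to acute stress". Section 2, Objectives, makes the relation between trait and HPA-axis reactivity one specific objective and the neuroendocrine response to a stress event after training another.
- **Analysis.** The Statistical analysis section assigns "ANOVA to evaluate between groups differences" and names no covariate. Mindfulness, trait and state, appears only in a list of variables for Spearman correlations. A further line plans correlation and multivariate analysis for plasma and behavioural markers. It does not mention saliva or any covariate.

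The Participants paragraph describes randomisation to two groups without stratification or balancing on trait.

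**The concern.** A randomised comparison usually draws its precision from the outcome's own baseline. Salivary cortisol has none here. The pre-stress sample is taken on day 3, once training is under way, so it is a reference for reactivity and not a pre-training baseline; training may already have moved it.

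The next best covariate is a pre-randomisation variable related to the outcome. The protocol names one, plans to measure it, and then leaves it out of the arm comparison. Two things follow if trait is related to day-3 cortisol. The variance that trait explains stays in the error term. And with 20 to 25 people per arm, any chance difference in trait carries over into the estimated training effect. Both fall on the outcome that serves the neuroendocrine objective.

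**Working it through.** **Inputs from the protocol.** 50 recruited, at least 40 needed; two groups (1:1 assumed, as no ratio is stated); f = 0.3; "at α = 0.05 and 80% of power"; "60% correlation between repeated measures"; test for sizing "RM-ANOVA with intra-between interaction".

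**Input not in the protocol.** r, the within-arm correlation between day-1 trait and the cortisol quantity analysed. A range of 0.2 to 0.5 is assumed.

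**1. The plan's own figure.** For the within-between interaction with m measurements, the noncentrality is f²·N·m/(1 − ρ). The stated inputs then need N = 20 (m = 2), 16 (m = 3) or 14 (m = 4) in total. For m = 2 and N = 20: 0.09 × 20 × 2 / 0.4 = 9, power 0.81. The figure of 40 is not reproduced. That is a separate matter; 40 and 50 serve below only as the numbers analysed.

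**2. Chance imbalance in trait.** In SD units, the SD of the difference between arm means is √(4/N).

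| N | SD of difference | P(\|diff\| > 0.3) | P(\|diff\| > 0.5) |
|---|---|---|---|
| 40 | 0.316 | 0.34 | 0.11 |
| 50 | 0.283 | 0.29 | 0.08 |

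An imbalance D shifts the unadjusted cortisol difference by r·D. At D = 0.5 the shift is 0.10 SD (r = 0.2), 0.15 SD (r = 0.3) or 0.25 SD (r = 0.5).

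**3. Type I error of the unadjusted test.** In simulation with N = 40 it is 5.0% over all randomisations, for r = 0.3 and for r = 0.5. Among randomisations with an imbalance above 0.5 SD it is about 8% (r = 0.3) or 13% (r = 0.5).

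**4. Precision.** Adjustment multiplies the residual variance by 1 − r², which is worth an unadjusted sample of N/(1 − r²). For illustration, take one two-arm contrast at d = 2f = 0.6. Power comes from the noncentral t with noncentrality [0.6/√(1 − r²)]·√(n/2), n per arm, on N − 2 degrees of freedom unadjusted and N − 3 adjusted.

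| r | 1 − r² | N = 40 worth | Power, N = 40 | N = 50 worth | Power, N = 50 |
|---|---|---|---|---|---|
| unadjusted | 1 | 40 | 0.46 | 50 | 0.55 |
| 0.2 | 0.96 | 41.7 | 0.47 | 52.1 | 0.56 |
| 0.3 | 0.91 | 44.0 | 0.49 | 54.9 | 0.59 |
| 0.4 | 0.84 | 47.6 | 0.52 | 59.5 | 0.62 |
| 0.5 | 0.75 | 53.3 | 0.57 | 66.7 | 0.67 |

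**5. Which term does the work.** Write person i's cortisol at time t as μ(t) + arm terms + b·x(i) + error, with x the day-1 trait. The change from the pre-stress sample contains b·x(i) − b·x(i) = 0. With complete data, a trait main effect therefore drops out of arm × time and sharpens only the average-level contrast. In a simulation with 20 per arm and four samples, adding it left all three arm × time estimates and their standard errors (0.2938) unchanged. If trait acts on reactivity, the slope is b(t), the change contains [b(t) − b(0)]·x(i), and only a trait × time term removes it.

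**The case against.** The strongest case against is that an unadjusted ANOVA in a randomised trial is valid, and that naming prognostic covariates is commonly left to a statistical analysis plan, which may exist but is not shown. The first part stands in full. The second does not dispose of the point: the protocol does state its between-arm method, and that method ignores a baseline score that its own rationale ties to the outcome.

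Several stronger readings are tempting and are not supported:

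- *That the false-positive rate is inflated.* Overall it stays at 5%; the excess in step 3 holds only given an unlucky allocation.
- *That trait drives cortisol.* The Introduction speaks of an association and an apparent influence, it cites a review that could reach no common conclusion on mindfulness practice and cortisol, and the Objectives treat the trait-reactivity relation as something to verify.
- *That the trial has only about 50% power.* Those figures belong to a single contrast with f converted to d = 0.6. The protocol sized a repeated-measures interaction, for which step 1 shows no shortage.
- *That saliva is the only measure tied to the stressor.* The Objectives also plan EEG during the stress test. Saliva is the only cortisol measure so timed.
- *That day-1 blood cortisol can stand in for the missing baseline.* It is a fasting, rested morning value, and nothing in the protocol links it to stress reactivity.

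It is also fair to say that the pre-stress sample is a proper reference for reactivity. It is, but it does nothing about trait imbalance between the arms.

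**Conclusion.** The point holds as a recommended improvement to a valid analysis. The planned comparison forgoes a baseline covariate that is already collected and that the protocol associates with the outcome. The cost is 4-25% of residual variance for r between 0.2 and 0.5. The estimate is also left exposed to a trait imbalance above 0.5 SD in roughly one trial in nine (20 per arm) to one in thirteen (25 per arm).

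The size rests on the assumed r. Up to about 0.3 the gain in power is small (at most 0.03 to 0.04); it becomes material from about 0.4 to 0.5. It also rests on 1:1 allocation, on the mindfulness scales being among the day-1 questionnaires, and on the wording of the saliva sections, since the timeline figure is not available in the text.

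**What to change.** In the Statistical analysis section, state that the arm effect on day-3 salivary cortisol comes from a linear mixed model with arm, sampling time, arm × time, the day-1 score of one prespecified trait scale (for example MAAS total), and trait × time. A simpler route to the same end is an ANCOVA of one prespecified reactivity summary per person on arm and day-1 trait.

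Use day-1 trait scores only. The questionnaires are repeated during and after the intervention, and those later scores may themselves be changed by training. Naming the scale in advance also closes off a later choice between the MAAS total and the five FFMQ facets. Day-1 blood cortisol may be added but is optional.

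With four sampling times the mixed model spends four degrees of freedom on trait (one for the main effect, three for trait × time); the ANCOVA spends one. No new visit, sample or participant is needed. The change adds no pre-training saliva value; it makes use of the baseline information that exists.

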**2. Objectives**

General:

• Assess the impact of a brief training on the stress response, interoception and well-being on healthy individuals.

Specific:

• Verify the relationship between mindfulness trait and hypothalamic-pituitary-adrenal axis reactivity.

• Analyze the neuroendocrine response to a stress event after a brief mindfulness-based intervention.

• Assess the impact of mindfulness practice (3 days) on the attention system, autonomic nervous system, and interoceptive ability.

• Check the influence of the practice on self-report measures of stress, anxiety, and affect

• Assess participants' electroencephalographic activity before and after the proposed intervention, during a sustained attention test, an interoception test, and during the stress test.

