**Blood collection:**

Study participants will undergo venipuncture of 20 ml of blood after fasting for 8 hours before and after the intervention proposed in this project. They will be instructed to have a peaceful night's sleep and to attend the collection point at the agreed time. Blood collection will be carried out in the non-dominant arm of each participant, in the morning (between 8:00 and 9:30 am) after 45 minutes of the participant's rest. Peripheral blood samples will be collected without anticoagulant (10 mL) to study the hematological, lipid, hepatic and renal profiles and the endocrine marker (cortisol) and BDNF.

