**Questionnaires**

The questionnaires described below will be applied before, during and after the interventions.

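### Spearman correlations among questionnaire measures carry no term for arm or time point, so pooling post-training scores would mix the arm difference into the association

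*Protocol*

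**What the plan says.** The Statistical analysis section states that a Spearman "correlation test will also be applied to test the occurrence of correlations between variables (anxiety, affect, stress and mindfulness, trait and state". It does not mention arm, stratification or the assessment to be used. A separate sentence covers other markers: "For the analysis of plasmatic and behavioral markers, correlation tests and multivariate analysis will be used". Neither the correlation tests nor the covariates are named there.

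Four other places bear on this:

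- Participants: after screening, "they will be randomized into two groups proposed in this study". The Training section makes these a recorded breathing practice and a colouring task.
- Questionnaires: "The questionnaires described below will be applied before, during and after the interventions".
- Risk and Benefit Assessment: anxiety, depression and perceived stress are expected to improve with practice. The Objectives add affect to the self-report measures on which an influence of practice is sought.
- Objectives, first specific objective: "Verify the relationship between mindfulness trait and hypothalamic-pituitary-adrenal axis reactivity". On the cortisol side, "Salivary cortisol dosages will be performed from samples collected on day 3 of the protocol", which is the last day of training. Blood is drawn by "venipuncture of 20 ml of blood after fasting for 8 hours before and after the intervention proposed in this project".

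**The concern.** An ordinary Spearman coefficient has no place for a covariate. The variables listed include state measures, and at least some of them are ones the protocol expects training to change. If scores taken after training are correlated over all participants, two measures that both respond to training will correlate because one group sits higher or lower on both, even if they are unrelated among people given the same intervention. If the arm shifts run against the sign of a real association, they weaken or hide it.

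At stake is how a significant or non-significant correlation at the 0.05 level can be read: as a relation between characteristics of people, or as a second appearance of the group difference that the ANOVA already tests.

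**Working it through.** The protocol gives no sample size, expected coefficient or power for the correlations, so there is no figure of its own to reproduce.

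**Inputs.** From the protocol: 50 recruited, at least 40 needed, two arms, significance level 0.05. Assumed, because not stated: equal allocation, two-sided tests, normal data, arm shifts of 0.6 to 1.0 within-arm SD, and a within-arm correlation of 0 or −0.4.

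**Formula.** For two equal arms with within-arm correlation r and arm shifts dx and dy (in within-arm SD), the correlation over all participants is

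r_pooled = (r + dx·dy/4) / √[(1 + dx²/4)(1 + dy²/4)].

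This is the product-moment value. The simulated mean Spearman coefficients follow it closely when r = 0 and lie about 0.02 to 0.03 nearer zero when r = −0.4.

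**1. Created association** (r = 0, both measured after training, shifts of opposite sign):

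- 0.6 SD: −0.09/1.09 = −0.083
- 0.8 SD: −0.16/1.16 = −0.138
- 1.0 SD: −0.25/1.25 = −0.200

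Rejection rates in 10,000 simulated trials per setting, where the correct rate is 5%:

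| Shift in both | Pooled, N = 50 | Adjusted for arm, N = 50 | Pooled, N = 40 | Adjusted for arm, N = 40 |
|---|---|---|---|---|
| 0.6 SD | 8.9% | 5.1% | 7.8% | 4.6% |
| 0.8 SD | 16.2% | 5.0% | 13.2% | 5.0% |
| 1.0 SD | 29.8% | 5.2% | 24.7% | 5.2% |

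**2. Hidden association** (r = −0.4, both measured after training and shifted the same way):

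- 0.6 SD: (−0.4 + 0.09)/1.09 = −0.284
- 1.0 SD: (−0.4 + 0.25)/1.25 = −0.120

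At N = 50, power is 46% and 8.6% pooled, against 77% and 76% adjusted. At N = 40 it is 38% and 7.6%, against 67% and 66%.

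**3. Baseline trait against a post-training outcome** (dx = 0 in expectation, by randomisation):

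- With r = 0 the numerator is 0, so nothing is created. Simulated pooled rejection is 4.9% to 5.3%.
- With r = −0.4 and an outcome shift of 0.6 SD: −0.4/√1.09 = −0.383. At 1.0 SD: −0.4/√1.25 = −0.358.
- Power at N = 50: 75.7% pooled against 78.6% adjusted at 0.6 SD, and 67.7% against 77.9% at 1.0 SD. Separate runs with r = +0.4 gave 75% against 78% at 0.6 SD, the same within simulation error.

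**4. Limit of the adjustment.** With r = −0.4 in one arm and +0.4 in the other and no shift, pooled and adjusted tests both reject about 5% of the time. Adjusting for arm does not detect opposite slopes.

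**The case against.** The strongest reply is that pooling is inferred from silence. Correlations within arm or at baseline also fit the text, and a statistical analysis plan may settle the time point and covariates. This stands as a caution, and the size of the problem is therefore conditional. It does not remove the point: the protocol itself names an unadjusted two-variable test, and the sentence before it does say which tests are within and between groups.

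The shift sizes are assumptions. A reader might take 0.6 SD to be the plan's own effect size, since f = 0.3 for two equal groups corresponds to it. The Participants section gives f for a repeated-measures within-between interaction, not for a difference in post-training scores, so the documents do not support that reading. Shifts near 1 SD are also harder to believe for scales that look back over weeks or a month, as the protocol describes for affect and perceived stress. State scales could move more.

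A reader might also infer that the cortisol correlations are planned as plain Spearman tests and that the first specific objective could be manufactured or cancelled by arm. Cortisol is not in the Spearman list. It falls at most under the unnamed correlation tests and multivariate analysis, and the latter could include arm. The protocol has pre-intervention questionnaires on day 1, and a day-1 trait score is independent of arm. The 3-day study cited in the Introduction, in which higher baseline trait went with lower reactivity while "the group undergoing mindfulness practice had, in general, an increase in the level of salivary cortisol", does not show masking, since both findings were reported. Nor do the documents say that the correlations would be presented as a mechanism; no mediation analysis is planned.

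Finally, a pooled correlation is a legitimate description of the mixed sample. It answers a different question, though, and its value depends on the arm effect and the allocation ratio.

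**Conclusion.** The point holds for the questionnaire correlations when post-training scores are pooled over arms. Under the stated assumptions the false-positive rate at N = 50 is about 9% to 30% rather than 5%, for shifts of 0.6 to 1.0 SD in both variables. A real negative association can be masked if both shifts go the same way. Where training moves one measure up and the other down, the shift instead creates or exaggerates a negative association. The effect needs both variables to respond to training; if only one does, power is lost but nothing is created.

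For the trait–HPA objective with a day-1 trait score, the consequence is only loss of power: about three points at 0.6 SD and ten at 1.0 SD. The ANOVA comparisons between groups are unaffected. This is more than a missing detail, because the test named gives a biased answer on scores the protocol collects, and a better one is available from the same data.

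**What to change.** State in the protocol which assessment each correlation uses. For any correlation with a measure taken after training starts, replace the plain test by a partial Spearman correlation adjusted for arm: rank over all participants, centre the ranks within arm, correlate, and test on N − 3 degrees of freedom instead of N − 2 (47 instead of 48 at N = 50).

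For the trait–HPA objective, name the day-1 trait score and day-3 cortisol reactivity, put arm in the model, and report the arm-by-trait term as exploratory, since adjustment alone misses opposite slopes.

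The cost of the adjustment is one degree of freedom and one line of analysis. No new data are needed.
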